### Blinding

A statistician unaware of the study, responsible for designating codes to the participants and allocation of groups, will prepare the packets of treatment regime for all the participants with day-wise dosage enclosed in separate opaque envelops and the unique code of the participants mentioned on it, blinding the participants and the investigator of the study. The treatment to all the participants will be given in separate rooms, and the parents of all the participants will be advised not to acquainted and communicate with each other after randomization for reducing the subjective biases. Blinding will only be permissible in case of withdrawal or termination of any study participants.

### Interventions

The detailed dietary intervention that will be provided to the participants recruited to each group is given in Table 2.

**Table 2 Tab2:** Intervention for study groups

*Participant group/arm*	*Intervention/treatment*
Placebo comparator: healthy controls (starch) The healthy controls will be given starch packed in the same way as the active prebiotics	**Dietary supplement: starch only** The starch solution is a low-fat diet **Dosage:** A daily dosage of 4 g of starch mixed with water or milk
Experimental: malnutrition (RUTF plus prebiotics) The malnutrition group with RUTF and prebiotic only. The RUTF will be given as per the WHO guidelines	**Dietary supplement: prebiotic galactooligosaccharide (GOS) Powder** Prebiotic GOS powder is a galactooligosaccharide ingredient low in mono-sugars. Scientific studies have shown positive effects of oligosaccharides, among which GOS, on growth of bifidobacterial, stool consistency bowel function and transit time, support of natural defenses and mineral absorption The product mainly consists of 97% dry matter with 69% prebiotic GOS, 23% lactose, and 5% glucose and galactose as monosaccharides. These prebiotics have β-(4) glycosidic linkages and have been proven as safe product **Dosage:** In this arm, participants will receive a daily dosage of 4 g of prebiotic GOS mixed with milk or water along with RUTF. The dosage of RUTF will be determined based on the weight of the child in such a way that two sachets will be given to a child with a weight of 5–6.9 kg in a day/week, three sachets to a child weighting 7–9.9 kg in a day/week, and four sachets were given to a child with having weight less than or equal to 10 kg in a day/week
Active comparator: malnutrition (RUTF plus starch) The malnutrition group with RUTF and starch only. The RUTF will be given as per the WHO guidelines	**Dietary supplement: RUTF plus starch** RUTF and the starch solution **Dosage:** In this intervention arm of the trial, participants will receive a daily dose of 4 g of starch mixed with milk or water along with RUTF. The dosage of RUTF will be determined based on the weight of the child in such a way that two sachets will be given to a child with a weight of 5–6.9 kg in a day/week, three sachets to a child weighting 7–9.9 kg in a day/week, and four sachets were given to a child with having weight less than or equal to 10 kg in a day/week

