### Study population and eligibility criteria

All children suffering from SAM, without any complications, and aged 6–59 months, are eligible for inclusion in the present trial. Participants will be screened using weight-for-height/length *z*-score and mid-upper arm circumference (MUAC) as screening criteria. The criteria of the World Health Organization (WHO) will be used to diagnose edema among children. WHO defines children with grade 1–2 bilateral edema and a weight-for-height/length *z*-score of < − 3 standard deviations (SD) or MUAC of < 11.5 cm who are otherwise clinically healthy, aware, and with a decent appetite as children with SAM [28]. Trained healthcare staff including nurse, childcare worker, and doctor will assess the children for eligibility. MUAC will be assessed using WHO’s MUAC colored tapes in centimeters (cm), while weight-for-height/length *z*-score and weight of children will be assessed in grams (g) with minimal and light clothing using UNISCALE, and height will be measured using a standard measuring tape in cm(s) and then will be compared with the grading of *z*-score chart. All the anthropometric measures will be taken thrice to reduce information bias. Additionally, all the instruments that will be used for taking measurements will be checked for accuracy and zero precision beforehand. All eligible participants will be recruited following a pre-defined inclusion and exclusion criteria (Table 1).

**Table 1 Tab1:** Inclusion and exclusion criteria

*Inclusion criteria*	*Exclusion criteria*
Ages 6–59 months at enrolment	
Acute malnutrition without complications, as defined by the WHO (i.e., children with MUAC < 115 mm or weight-for-height *z*-score < − 3 or grade 1–2 bilateral edema who will be clinically well and alert with good appetite	Presence of any complications of severe malnutrition (severe dehydration, severe anemia, severe pitting edema, anorexia, hypothermia, high pyrexia, acute lower respiratory infection, or hypoglycemia) or immune compromised
Parental consent for the child to participate	Declined parental consent
Healthy children without any chronic or acute illness	Children on antibiotic treatment for any disease in the last 3 months

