### Withdrawal and termination criteria and management

RUTF will be provided as per the guidelines of WHO and all the therapies allowed by WHO will be permitted during the trial. However, children showing poor compliance or absence from two consecutive follow-up visits will be withdrawn from the study, while those showing any allergies or adverse events will be terminated from the study, and appropriate treatment will be provided to them after proper investigation by the principal investigator.

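### Table 2 misprints the RUTF dosing rule in both SAM arms: the four-sachet band is almost certainly reversed, and the dosing period is left as day or week

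*Protocol article*

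**What the plan says.** Table 2 (Protocol article, Interventions) gives the same weight-based RUTF rule for the experimental arm and the active comparator arm. It has three bands:

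- The first band reads: "two sachets will be given to a child with a weight of 5–6.9 kg in a day/week"
- The second band reads: "three sachets to a child weighting 7–9.9 kg in a day/week"
- The third band reads: "four sachets were given to a child with having weight less than or equal to 10 kg in a day/week"

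Each arm's entry also says "The RUTF will be given as per the WHO guidelines", and the section on withdrawal and termination repeats that "RUTF will be provided as per the guidelines of WHO". Neither place gives the WHO quantities.

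The supplement in the same table has a clear period: in the experimental arm "participants will receive a daily dosage of 4 g of prebiotic GOS mixed with milk or water along with RUTF", and starch is likewise daily. The Blinding section describes treatment packets "with day-wise dosage enclosed in separate opaque envelops" but does not say whether RUTF is inside them.

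Eligibility (Table 1) rests on "Ages 6–59 months at enrolment" together with MUAC, weight-for-height z-score or edema. There is no lower or upper limit on body weight.

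**The concern.** The three bands cannot all apply. The third is written as an upper limit on weight where the sequence calls for a lower limit, so it covers the first two bands and excludes the heavier children it was presumably meant for. The inequality is spelled out in words and appears in both arms, so a symbol lost in typesetting does not explain it.

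The period is a second, independent defect. All three bands are expressed per day/week, which could mean either.

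RUTF is the core treatment for severely malnourished children, and the table presents these numbers as the rule to apply. Staff who worked from the table rather than the WHO guideline could misdose individual children. That would matter first for the child. It would also add noise to weight-for-height, MUAC and body composition, which are secondary outcomes. Nor could another group reproduce the background treatment from this text.

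**Working it through.** **Inputs.** Bands and sachet counts come from Table 2. The 8-week duration (56 days) comes from Randomization and allocation. Weights are taken to 0.1 kg, as the band limits imply.

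**Step 1: apply the rule as printed and with the third band reversed.**

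| Weight | Sachets, as printed (third band ≤ 10 kg) | Sachets, third band ≥ 10 kg |
|---|---|---|
| under 5 kg | 4 | none stated |
| 5–6.9 kg | 2 and 4 | 2 |
| 7–9.9 kg | 3 and 4 | 3 |
| exactly 10 kg | 4 | 4 |
| above 10 kg | none stated | 4 |

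As printed, exactly 10 kg is the only weight from 5 kg upward with a single dose. With the inequality reversed, every weight from 5 kg upward has one dose, and the dose rises with weight. The gap below 5 kg then becomes visible. Nothing in the eligibility criteria keeps such a child out.

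**Step 2: sachets per kg = sachets ÷ weight, third band reversed.**

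- 5–6.9 kg: 2/5 = 0.40 down to 2/6.9 = 0.29
- 7–9.9 kg: 3/7 = 0.43 down to 3/9.9 = 0.30
- 10 kg: 4/10 = 0.40

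The two lower bands cover nearly the same range, and the third starts inside it. This pattern supports the reversed-inequality reading without any outside source.

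**Step 3: sachets per kg if four sachets were given as printed.**

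- 5–6.9 kg: 4/5 = 0.80 down to 4/6.9 = 0.58, which is 4/2 = 2 times the two-sachet dose
- 7–9.9 kg: 4/7 = 0.57 down to 4/9.9 = 0.40, which is 4/3 = 1.33 times the three-sachet dose
- under 5 kg: more than 4/5 = 0.80

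These are the extremes of a literal reading, not expected variation.

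**Step 4: the period.** Total over the trial = sachets × 56 if daily, or sachets × 8 if weekly.

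| Sachets per period | Daily | Weekly | Ratio |
|---|---|---|---|
| 2 | 2 × 56 = 112 | 2 × 8 = 16 | 7 |
| 3 | 3 × 56 = 168 | 3 × 8 = 24 | 7 |
| 4 | 4 × 56 = 224 | 4 × 8 = 32 | 7 |

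The daily supplement and the day-wise packets both favour the daily reading. Neither states it for RUTF.

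**The case against.** The best defence is that this is a slip with an obvious meaning. The bands ascend, the sachet counts ascend, and only 10 kg or more fits. A nurse facing a 6 kg child would see two conflicting doses and check rather than silently give the wrong one. The document says in each SAM arm and again under withdrawal criteria that RUTF follows WHO guidelines. Staff receive two days of training and children are monitored weekly for safety. This is a journal article, the full protocol is available on request, and the site dosing instructions are not shown, so they may well be correct. The weekly reading is unlikely, so the sevenfold range does not describe doses that will be delivered. The gap below 5 kg appears only once the third band is corrected, and the WHO guideline may already cover it.

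Much of this stands. The intended meaning is probably clear, the practical risk is limited, and the dose figures bound a literal reading without forecasting anything. But the WHO reference does not repair the table. The document gives no WHO quantities, the only numbers on the page are the contradictory ones, and nothing says which source prevails. Nor can condensation excuse it: the article chose to print a specific rule and printed it wrongly. The gap below 5 kg is secondary, but it should be closed when the band is corrected, because such children are eligible.

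**Conclusion.** The concern holds. The printed rule is internally contradictory in both SAM arms, and its period is not fixed. If followed literally, it allows twice the two-sachet dose at 5–6.9 kg, a third more than the three-sachet dose at 7–9.9 kg, and no stated dose above 10 kg. The period wording leaves at most a sevenfold range, with daily the more likely meaning.

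That the third band should read 10 kg or more is an inference from the order of the bands and the per-kg pattern. The WHO guideline itself was not available to confirm it. How many children would be misdosed, if any, cannot be estimated from the document.

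The consequence is bounded. The wording is identical in both arms and allocation between them is random, so no bias in their comparison is claimed, and no effect on the primary microbiome outcome is claimed. What remains is the safe and reproducible delivery of the background treatment, and possible extra variability in the growth and body-composition outcomes. It should be fixed because it is an operative dosing rule for sick young children.

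**What to change.** Check the WHO guideline that the protocol follows, then in Table 2, for both SAM arms:

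- change the four-sachet band to its intended limit, most likely 10 kg or more;
- replace day/week with one period, most likely per day;
- add a quantity or a rule for children under 5 kg;
- state that the WHO guideline prevails if the two ever differ.

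Confirm that the site dosing instructions carry the corrected rule. As an optional clarification in the experimental arm, say whether the 4 g refers to the powder. If so, at the stated 69% it contains 4 × 0.69 = 2.76 g of GOS.

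The cost is a few words in two table entries and a check of the site instructions, with no extra children, visits or procedures.

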### Withdrawal and termination criteria and management

RUTF will be provided as per the guidelines of WHO and all the therapies allowed by WHO will be permitted during the trial. However, children showing poor compliance or absence from two consecutive follow-up visits will be withdrawn from the study, while those showing any allergies or adverse events will be terminated from the study, and appropriate treatment will be provided to them after proper investigation by the principal investigator.

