### Adverse events and safety monitoring

Throughout the trial, participants will be monitored on weekly basis to ensure safety. In case of any allergic reactions or adverse events, prognostic treatment will be provided after proper investigation free-of-cost. Further, participants will be encouraged to report to and contact the designated personnel in case of any discomfort or adverse event 24/7 to ensure the reporting and treatment of adverse events within 24 h. The principal investigator will then decide the continuation of the trial treatment after excluding for the factor unrelated to the trial medications. There are no anticipated harms of the interventions of the present trial; therefore, no post-trial care and compensation has been planned for participation in the present trial.

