### Strategies for improving adherence

For improving the adherence of the trial, contact numbers of the parents of the participants will be collected, and a daily reminder text/call will be dropped. Empty treatment packets will not be collected for ensuring the blinding of the study. In addition to this, the parents of the participants will be incentivized through multi-vitamins for their other children and family members.

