### Statistical analysis

Intention-to-treat (ITT) analysis will be used in the present trial for analyzing the results. All the participants who are randomized, received at least one intervention, and evaluated for at least one outcome will be analyzed with missing data substituted according to the principle of ITT.

For evaluating the microbiome diversity, Ribosomal Database Project (RDP) Bayesian algorithm will be used to identify microbial structure at phylum and genus level among samples and trial groups using Fast Length Adjustment of Short Reads (FLASH) version 1.2.11 and software R version 3.4.1.

Raw sequence data will be filtered to obtain high-quality clean data with DADA2, after which clean reads that overlapped each other will be merged into tags and clustered to operational taxonomic units (OTU). Taxonomic classifications will be assigned to OTU representative sequences using the RDP database. FLASH version 1.2.11 will be used for generating consensus sequences for paired-end reads, and software R version 3.4.1 will be used to create phylum and genus abundance bar plots. Further, alpha diversity analysis will also be conducted. Alpha diversity is the analysis of species diversity in a sample, measured by observed species index, Chao1 index, Shannon index, Simpson index, and good-coverage index.

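### Children are removed from the study for poor compliance or adverse events, yet the analysis is called intention-to-treat: week-8 outcomes can be lost for treatment-related reasons and replaced by an unnamed substitution

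*Protocol article*

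**What the plan says.** - **Removal (Withdrawal and termination criteria and management).** Two rules apply after randomisation: "children showing poor compliance or absence from two consecutive follow-up visits will be withdrawn from the study", and "those showing any allergies or adverse events will be terminated from the study". Both concern leaving the study, not only the supplement.
- **Adverse events (Adverse events and safety monitoring).** The rule here differs: "The principal investigator will then decide the continuation of the trial treatment after excluding for the factor unrelated to the trial medications".
- **Timing (Data collection, Table 5).** Stool, anthropometry, MDAT and body composition are scheduled at week 0 and week 8 only. No sampling after withdrawal is described.
- **Analysis (Statistical analysis).** "Intention-to-treat (ITT) analysis will be used in the present trial for analyzing the results". The set is defined as "All the participants who are randomized, received at least one intervention, and evaluated for at least one outcome", with "missing data substituted according to the principle of ITT".
- **Sample size (Sample size estimation).** 53 per arm, raised by 10% to 58. The reason given for the 10% is loss to follow-up; removals required by the protocol are not mentioned.

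**The concern.** Intention-to-treat means that each randomised child is analysed in the assigned arm, whatever happens to adherence or tolerance. A rule that removes children from the study for non-adherence or an adverse event works against that, because it ends outcome collection for reasons that may differ between GOS and starch. With a single post-baseline time point, a child who leaves early contributes nothing observed after randomisation.

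The analysis section does not repair this. A set that needs at least one intervention and one evaluated outcome is a modified ITT set. ITT settles who is analysed; it does not say how a missing value is filled. If a baseline measurement counts as an evaluated outcome, early leavers could enter the analysis with week-8 values that are wholly substituted. If it does not, they drop out and the comparison is between children who complied with and tolerated their product.

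At stake is the only randomised contrast in the trial, GOS versus starch on top of RUTF: bias in its estimate, and either lost power or a wrong error rate. A later analysis plan cannot recover outcomes that were never collected.

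**Working it through.** **Inputs from the article:** k = 3, f = 0.25, alpha = 0.05, power 80%, 53 per arm, 10% inflation, 58 per arm. The article gives no adverse-event, compliance or removal rates, so every loss rate below is an assumption.

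**1. The plan's own figure.** One-way ANOVA power from the noncentral F with noncentrality 3n × f². At n = 53 this is 159 × 0.0625 = 9.94 and power is 0.805; at n = 52 it is 0.797. So 53 reproduces. Inflation: 53 × 1.1 = 58.3, taken as 58. With 10% lost, 58 × 0.9 = 52.2 remain (power 0.798), so the allowance is used up at 10%.

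**2. Scenario A: removed children are not analysed.**

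| Loss per arm | Observed per arm | Omnibus power at f = 0.25 |
|---|---|---|
| 0% | 58 | 0.842 |
| 10% | 52.2 | 0.798 |
| 20% | 46.4 | 0.746 |
| 30% | 40.6 | 0.683 |

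**3. Scenario B: removed children are kept with substituted values.** This is an alternative to A; the two sets of figures cannot both apply to one analysis. Take the planned three-arm ANOVA with n = 58 per arm, o of them observed, random loss and no true effect. Own-arm-mean substitution leaves the arm means and the within-arm sum of squares unchanged but counts n children instead of o. The nominal F is therefore the valid F multiplied by n(n−1)/[o(o−1)], and the true type I error is P[F(2, 3(o−1)) > 3.049 × o(o−1)/(58 × 57)], where 3.049 is the 5% critical value of F(2, 171).

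| Missing | o | Effective cut-off | True type I error |
|---|---|---|---|
| about 10% | 52 | 3.049 × 0.802 = 2.446 | 0.090 |
| about 20% | 46 | 3.049 × 0.626 = 1.909 | 0.152 |
| about 30% | 41 or 40 | 1.512 or 1.439 | 0.22 or 0.24 |

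By simulation (20,000 trials), overall-mean substitution, and baseline carried forward under equal random loss, both stay at about 0.05 for all three loss rates.

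**4. Bias in the randomised contrast.** If a fraction p of an arm is removed and those children are d SD below the children who stay, the observed mean exceeds the full-arm mean by p × d. With d = 0.5 and 20% versus 5% removed, the contrast shifts by (0.20 − 0.05) × 0.5 = 0.075 SD. A harsher case is 20% removal in the GOS arm correlated 0.5 with poor outcome, against 10% random loss in the starch arm. Simulation then gives a false benefit of about 0.18 SD, both for complete cases (two-arm rejection rate 0.15) and for own-arm means (0.23). The standard error with 58 per arm is √(2/58) = 0.186 SD. Baseline carried forward errs in another way: if both arms improve by 0.8 SD and random loss is 20% versus 10%, the shift is −(0.20 − 0.10) × 0.8 = −0.08 SD.

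**5. Reach of the literal adverse-event rule.** With an assumed weekly risk r, the share affected by week 8 is 1 − (1 − r)⁸: 15%, 34% and 57% for r = 2%, 5% and 10%. These figures hold only if the termination rule is applied without the discretion given in the adverse-events section.

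**The case against.** Several points on the other side stand.

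- A reader might infer that every child with any adverse event leaves the trial. The termination rule says so taken alone, but the adverse-events section leaves continuation of treatment to the principal investigator. The documents support a contradiction between the two sections, not the certainty of universal removal. Diarrhoea and respiratory infection are listed as symptoms in SAM children without frequencies, and acute lower respiratory infection and severe dehydration are exclusions at entry, so no removal rate can be read from the text.
- A reader might infer that substitution necessarily understates error. No method is named. The inflation belongs to own-arm means and similar single-value fills; other methods hold 5% under random loss, and proper multiple imputation is designed to carry the uncertainty. The method may be in an analysis plan not shown, so its absence is not the finding. What is wrong as written is attributing substitution to ITT.
- Absence of week-8 data after removal is an inference from the wording and the schedule, not a statement in the article.
- Reading the word for randomisation in the set definition as shutting out the healthy group is too literal: the randomisation, outcome and analysis sections plainly include that group.
- The lack of a compliance threshold, and the decision that "Empty treatment packets will not be collected for ensuring the blinding of the study", are side points that a condensed article may leave to the full protocol.
- On the expected dates, recruitment ended on 31 July 2024 and follow-up eight weeks later, before publication on 26 November 2024. If those dates were kept, more sampling is no longer possible. They are expected dates only, and the analysis-set correction does not depend on them.

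None of this removes the conflict between the study-removal rules and the ITT label.

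**Conclusion.** The concern holds in this form: followed as written, the plan removes randomised children from the study for adherence and tolerance, gives them no week-8 outcome on the ordinary reading, and then labels a modified set intention-to-treat. The size is conditional.

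- If removed children are excluded, power falls from 84% to 80%, 75% or 68% at an assumed 10%, 20% or 30% loss.
- If they are kept, the three-arm type I error lies between about 5% and about 9%, 15% or 23% at those rates, depending on the substitution used.
- Bias in the GOS-versus-starch contrast is 0.075 to 0.18 SD in the two illustrations. The smaller is under half of one standard error and the larger about one standard error, so bias is possible but its size is not established.

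The two adverse-event rules contradict each other and must be reconciled. No view is taken here on which is right.

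**What to change.** 1. Without changing when the supplement is stopped, separate stopping the supplement from leaving the study. Seek the scheduled week-8 stool sample and measurements from every randomised SAM child unless consent is withdrawn.
2. Define the primary set for the SAM comparison as all randomised SAM children in their assigned arm. If the present set is kept, label it modified ITT.
3. Replace the wording on substitution with a named method: a likelihood-based model, or multiple imputation by arm using baseline values. Add a delta-shift sensitivity analysis that makes the imputed values of removed children progressively worse and reports where the conclusion changes.
4. Reconcile the adverse-event rule in the withdrawal section with the one in the safety section.

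Cost: rewording, some added follow-up contact and modest extra analysis. The week-8 visit already exists. Where follow-up has finished, item 1 is no longer possible and only the analysis-set and missing-data changes can be made; removals should then be reported by arm and reason.
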